### Allocation and randomisation

Prerandomisation eligibility checks will be carried out to ensure that participants are eligible for inclusion in the study. Patients will be randomly assigned to one of two groups (experimental or control) using a computer-generated random assignment in a 1:1 ratio. The computer randomly extracts 112 numbers from the 1–224 number as the hybrid fixation group, and the remaining numbers as the plate fixation group. According to the order of inclusion, patients will be numbered 1–224. Patients, researchers performing the follow-up measurements and the trial statistician will be blinded to the group allocations.

### Blinding

Blinding in this study is almost impossible. The surgical approach differs considerably between these two methods. All patients, researchers and surgeons can also see the differences in the skin incisions between the ESIN and ORIF treatments.

### Interventions

Surgical treatment will be performed either by or under the supervision of an experienced orthopaedic surgeon within 2 weeks after initial trauma.

#### Plate fixation group

A 3.5-mm narrow locking compression plate (DePuy Synthes, Raynham, MA, USA) will be the preferred choice of the treating surgeon. The length of the plate will be at least 7 holes to ensure stability of osteosynthesis, and at least three bicortical screws will be used on both sides of the fracture line. For dual plating fixation constructs, ORIF of the ulna will be performed using the direct approach to the subcutaneous ulnar shaft. The radius will be exposed with a standard anterior (Henry) approach. The dynamic compression plates will be used for both the radius and ulna. Reduction will be obtained and provisionally fixated; fluoroscopic image intensification will be used to verify rotational alignment and reduction of both fractures. Fixation of the implants will then be definitively secured.

#### Hybrid fixation group

The Titanium Elastic Nail System from Synthes (DePuy Synthes) with ESIN nails of 2.0–3.0 mm diameter, appearing to be one third of the diameter of the central bony canal, are usually used in our Department of Trauma Surgery. For hybrid constructs, the patient will be placed on the table and an image intensifier will be used to localise the placement of skin incisions. The radial ESIN nail is inserted through a 1- to 2-cm mini incision, to protect the superficial radial nerve, at the distal lateral radius. When the nail reaches the fracture site, the fracture is reduced by manipulation and traction under image intensifier control. Once reduction, alignment and provisional fixation of both fractures is satisfactory, the straight rod will be removed and an appropriately sized elastic intramedullary nail will be inserted into the radius. The plate on the ulnar will then be definitively affixed to the bone. An above-elbow plaster cast will be applied and maintained for 2 weeks.

### Outcomes

Clinical radiological evaluation of union, functional evaluation of outcome and rate of complications will be performed immediately, and at 2 weeks and 1, 3, 6 and 12 months.

#### Primary outcome measures

Primary outcome measures are DASH score and radiological evaluation:The primary outcome measure of this study is the DASH score, which will be recorded at 1, 3, 6 and 12 months postoperatively. The primary time point is at 12 months. DASH is a widely used and validated tool assessing upper extremity-related deficits and symptoms in daily life reported by the patient. It has been shown to be a valid instrument to monitor changes in symptoms and function over time [32–34].Radiological evaluation based on postoperative X-ray, including nonunion of the fracture and malunion of the fracture, will be performed at 2 weeks and 1, 3, 6 and 12 months postoperatively.

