**Methods:**

An RCT will be conducted, and the participants included will be randomly divided into either the hybrid fixation group or the double plate fixation group, at a ratio of 1:1. The primary clinical outcome measures are the Disabilities of the Arm, Shoulder and Hand score and radiological evaluation. Secondary clinical outcome measures are intraoperative blood loss, surgical duration, visual analogue scale score after surgery, hospital duration after surgery and complications. Follow-up will be conducted at 2 weeks and 1, 3, 6 and 12 months postoperatively.

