Both ORIF and ESIN fixation have their shortcomings. Therefore, we need to find another surgical treatment which can decrease the rate of complications and improve the clinical efficacy. Our study plans to test hybrid fixation, using an ESIN fixation for the radius, and open reduction and plate screw fixation for the ulna. Compared with double plate fixation, hybrid fixation not only reduces soft tissue dissection and potentially refracture rates after implant removal, but it also incorporates some advantages of ESIN fixation. Feng et al. conducted a case-control study and found that mixed fixation was a feasible method [29]. Our study will conduct a randomised controlled trial (RCT) comparing double plate fixation with hybrid fixation for treatment of both-bone forearm fractures in older children between 10 and 16 years of age.

The objectives of this trial are to compare the effectiveness between double plate fixation and hybrid fixation for treatment of both-bone forearm fractures in older children. Our hypothesis is that there is no clinically relevant difference in the primary outcome measures between the two treatment groups.

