### Sample size

The sample size calculation is performed using G*Power 3.1 [30] and is based on Disabilities of the Arm, Shoulder and Hand (DASH) score as the primary outcome measure in this trial. For the sample size calculation, we used an α level of 0.05 and a β level of 0.1. We assumed the minimal clinically important difference (MCID) of the DASH to be 5 points, with the standard deviation (SD) being 14.7 [31]. Using these assumptions, the required sample size is 98 per group with 90% power to show a clinically important difference between the treatment methods with a two-sided type I error rate of 5%. With an assumption of 12.5% lost to follow-up, we decided to include 112 participants per group.

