### Statistical analysis

The trial data will be analysed using SPSS for Windows software (V.19.0; SPSS, Chicago, IL, USA). For continuous variables, the Shapiro-Wilk test will be applied to determine if they follow a normal distribution. For normally distributed variables, the means will be calculated and compared using the independent samples *t* test (Student’s *t* test) or analysis of variance (ANOVA); otherwise, the Mann-Whitney *U* test will be used for group comparisons. The χ2 test will be used to analyse qualitative variables. In all analyses, *p* < 0.05 will be taken to indicate statistical significance.

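### The protocol names both one primary outcome (DASH) and two (DASH and radiological evaluation), and the radiological one has no single variable, primary visit or sample-size basis

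*Protocol article*

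**What the plan says.** Text that points to two primary outcomes:
- Abstract, Methods: "The primary clinical outcome measures are the Disabilities of the Arm, Shoulder and Hand score and radiological evaluation".
- Primary outcome measures, opening line: "Primary outcome measures are DASH score and radiological evaluation".
- Background, last paragraph, repeated in the abstract's Discussion, in the plural: "Our hypothesis is that there is no clinically relevant difference in the primary outcome measures between the two treatment groups".

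Text that points to one:
- Primary outcome measures, the very next sentence: "The primary outcome measure of this study is the DASH score, which will be recorded at 1, 3, 6 and 12 months postoperatively". The 12-month primary time point is stated inside this DASH item.
- Sample size: the calculation rests on the "Disabilities of the Arm, Shoulder and Hand (DASH) score as the primary outcome measure in this trial".
- Expectations: the same expectation of no relevant difference, now with outcome measure in the singular.

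The radiological item is described as including nonunion and malunion, assessed at 2 weeks and at 1, 3, 6 and 12 months. No visit is marked as primary for it. The Statistical analysis section sets one threshold for all analyses: p < 0.05 "will be taken to indicate statistical significance".

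**The concern.** Which outcome is primary determines what the 5% error rate protects and what the trial may conclude. Here that decision is made twice, with different answers, and no sentence says whether the conclusion rests on DASH alone, on either outcome or on both.

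The second named primary is also not yet an endpoint. It has more than one component, five possible visits, and no event rate or relevant difference behind it. Two consequences follow, depending on the reading:
- If either outcome may carry a claim of difference, the two-sided 5% in the sample size section no longer describes the trial.
- If the hypothesis of no relevant difference must hold on both, a non-significant comparison of uncommon radiological events could be taken as confirmation when the trial had little chance of finding a difference.

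**Working it through.** **Inputs from the article.** Two-sided alpha 0.05; p < 0.05 in all analyses; 98 per group needed; 112 per group enrolled with 12.5% loss; chi-square test for qualitative variables; radiology at five visits; DASH primary at 12 months. No radiological event rate is given, so the rates below are assumptions.

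**The plan's own figures.** The loss step reproduces: 98 / (1 − 0.125) = 112. The 98 does not follow from the stated inputs: 2 × (1.960 + 1.282)² × (14.7/5)² = 181.6, so 182 per group. That is a separate matter. Here 98 is simply the number the article expects to analyse.

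**Reading A: either outcome may carry a claim of difference.**
- Two independent tests of exact size 5%: 1 − 0.95² = 0.0975. This treats radiology as one test at one visit, which the article has yet to define.
- With correlated test statistics (simulation, assumed correlations): 9.5% at 0.3, 9.1% at 0.5, 7.8% at 0.8.
- With rare events the chi-square test falls short of its nominal size. Exact binomial enumeration at 98 per group, no continuity correction, gives size 3.9% at a 2% event rate and 1.3% at 1%. The two-test error is then 1 − 0.95 × 0.961 = 8.7%, or 1 − 0.95 × 0.987 = 6.2%.
- If the radiological visit were chosen after seeing all five, with one radiological variable plus DASH at 12 months: 1 − 0.95⁶ = 26.5% if independent, and about 22%, 19% and 15% at assumed between-visit correlations of 0.5, 0.7 and 0.9. These figures also take each test at full 5% size. The article does not say that each visit is tested, so this shows what an unnamed visit leaves open.

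**Reading B: both outcomes must show no difference.** There is no alpha inflation; the question is what a non-significant radiological result is worth. Exact power is the sum, over all pairs of event counts, of Bin(x; n, p1) × Bin(y; n, p2) wherever the uncorrected chi-square exceeds 3.841:

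| Assumed rates | n = 98 per group | n = 112 per group |
|---|---|---|
| 2% vs 5% | 18.2% | 20.5% |
| 5% vs 10% | 26.4% | 30.4% |

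So a doubling or more of an uncommon event would be missed about 70% to 82% of the time.

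**Reading C: DASH at 12 months alone.** One test at 0.05. The 5% stands and radiology cannot change the conclusion.

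**The case against.** The strongest reply is that the hypothesis is one of no difference, stated for the outcomes in the plural. Read plainly, it needs both outcomes to agree, so a chance p < 0.05 on one would count against the claim. This stands in part: reading A is not the one the text favours, and the 9.75% must stay conditional on it. But the hypothesis sentence is not a decision rule, the Expectations section uses the singular, and reading B has its own weakness in power.

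Second, the article already ranks the outcomes to some degree: DASH alone has a primary time point and alone sets the sample size. That also stands. A reader might infer that the trial has no defined answer at all; the text does not support that, because DASH at 12 months clearly anchors the design. What is unsettled is whether radiology shares that standing.

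Third, an alpha split or testing order may properly sit in a statistical analysis plan that is not shown. Agreed, and its absence is not the point. The point is that the article contradicts itself on how many primary outcomes there are.

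Finally, the event rates behind the power figures are assumed. Other rates would give other values, but the article offers none to use instead.

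**Conclusion.** The protocol is wrong as written on this point: it cannot have both one primary outcome and two, and the second lacks a single variable, a primary visit and a sample-size basis. The size depends on the reading. If either outcome may carry a claim of difference, the error is at most about 9.75% for two tests, lower with correlation or rare events, and higher if the radiological visit is picked afterwards. If both must show no difference, error is not inflated, but radiological power is about 18% to 26% at 98 per group under the assumed rates.

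A reader might infer that the plan involves eleven tests at 5% (DASH, plus nonunion and malunion at each of five visits) and hence a 43% error rate (1 − 0.95¹¹ = 0.431). The documents do not support this. The five visits are an assessment schedule, no test at each is planned, and the figure needs eleven independent tests of full size, whereas repeated readings of the same fractures are likely to be dependent and rare-event tests fall below nominal size.

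**What to change.** Name DASH at 12 months as the sole primary outcome in the abstract, the hypothesis and the outcomes section, in line with the sample size section. Make nonunion and malunion, each at 12 months, secondary outcomes reported as risk differences with 95% confidence intervals, and treat earlier radiographs as descriptive. State that a radiological p-value alone, significant or not, does not decide the trial's conclusion.

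Cost: radiology loses the primary label. Visits and data collection do not change, and this fix does not alter the sample size. Because recruitment began in October 2018, removing a named primary outcome is a substantive amendment. It must be posted in the registry, as the Protocol amendments section provides, before any outcome data are analysed. No interim analysis is planned, which makes that feasible.

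Keeping two either-or primaries at 0.025 each would cost more. On the article's own DASH inputs, 2 × (2.241 + 1.282)² × (14.7/5)² = 214.6, so 215 per group against 182 at 0.05, and radiology would still need its own variable, visit and assumed rates. Requiring both outcomes would also remove the ambiguity, but the trial would then have to be sized for radiology as well.

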#### Secondary outcome measures

Measurements are recorded at 2 weeks and 1, 3, 6 and 12 months postoperatively.Intraoperative blood loss will be recorded in the anaesthesia records and will include the blood in suction bottles (after subtracting the lavage fluid used during the surgery) and that in the weighed sponges used during the operation.Time of surgical duration.Pain at rest (0–10 score with visual analogue scale).Pain at activities (0–10 score with visual analogue scale).Range of motion (ROM) of elbow and wrist.Complications: wound infection, reoperations and nerve injury.Length of hospital stay after surgery.Cost-effectiveness.

### Data collection and management

Questionnaire forms on paper will be the primary data collection tools for the study. The questionnaires will be completed at the outpatient clinic during the baseline and control visits. On receipt of the questionnaire forms, the researcher will make a visual check of the responses and will query missing data when possible. The paper forms will be securely stored at both study sites. Double data entry will be used to minimise typing errors. A research nurse and a research assistant will enter the data independently into two separate electronic databases. First, the research nurse enters the data into an electronic database, which is located in a secure network drive and protected with access codes known only by the research nurse. Missing, implausible and inconsistent data in the electronic database will be checked by the research nurse at the coordinating centre. If a missing or implausible item is noticed, the patient will be contacted and asked about the item. The answer will be corrected on the original paper form with a note that the answer was retrieved by a phone call and the corrected data had been entered to the database.

Patient records in the participating hospitals will also be used when collecting missing data or interpreting inconsistent or implausible data. After 12 months follow-up visits are completed and all data stored, a research assistant, not involved in the trial, will enter all the data from the paper forms into a separate database. The two databases will be compared for consistency. Discrepancies will be checked from the original paper forms by a research nurse at the coordinating centre. Final interpretation of the data will be corrected into the master database, which will be the source for the final data analysis.

### Monitoring

#### Data monitoring

We will conduct the study without a data monitoring committee (DMC). Both treatment methods are widely used in daily practice and have been proven to provide acceptable results. Since there is no DMC, we will not conduct an interim analysis during the trial.

#### Harms auditing

All the medical records of the participating patients will be carefully assessed, and all harms and complications of the treatment will be reported when reporting the results of this trial. The harms will be categorised as serious and minor adverse events as described in the section.

#### Auditing

We will not conduct auditing between the participant centres during the trial.

### Follow-up

Follow-up will be conducted at 2 weeks and 1, 3, 6 and 12 months postoperatively.

### Statistical analysis

The trial data will be analysed using SPSS for Windows software (V.19.0; SPSS, Chicago, IL, USA). For continuous variables, the Shapiro-Wilk test will be applied to determine if they follow a normal distribution. For normally distributed variables, the means will be calculated and compared using the independent samples *t* test (Student’s *t* test) or analysis of variance (ANOVA); otherwise, the Mann-Whitney *U* test will be used for group comparisons. The χ2 test will be used to analyse qualitative variables. In all analyses, *p* < 0.05 will be taken to indicate statistical significance.

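### A Shapiro-Wilk pre-test chooses the primary analysis of 12-month DASH, and its non-normal branch plans only a Mann-Whitney p-value, with no estimate in DASH points to set against the 5-point MCID

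*Protocol article*

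**What the plan says.** The Statistical analysis section sets one rule for all continuous variables: "the Shapiro-Wilk test will be applied to determine if they follow a normal distribution". If a variable passes, means are calculated and compared by t test or ANOVA. If it fails, the Mann-Whitney U "test will be used for group comparisons". The only criterion for a conclusion is p < 0.05. The section names no effect estimate or confidence interval for the non-normal branch and makes no exception for the primary outcome.

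Under Primary outcome measures, DASH "will be recorded at 1, 3, 6 and 12 months postoperatively", and "The primary time point is at 12 months".

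The Sample size section takes the "minimal clinically important difference (MCID) of the DASH to be 5 points, with the standard deviation (SD) being 14.7", with a two-sided test at 5% and 90% power, and arrives at 98 per group (112 after allowing for loss). The aim is stated at the end of the Background and repeated in the Abstract and under Expectations: "Our hypothesis is that there is no clinically relevant difference in the primary outcome measures between the two treatment groups".

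**The concern.** Three parts of the protocol do not fit together. The sample size is built on a difference in means of 5 points. The hypothesis asks whether any difference is small enough not to matter clinically, and 5 points is the only figure the protocol gives for that. The analysis rule, however, moves the primary outcome from means to ranks whenever a normality test fails, and then plans a p-value only.

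DASH cannot fall below 0. If most children recover well by 12 months, scores will bunch near that floor and the normality test will fail. The trial would then report whether ranks differ significantly, which does not say whether the difference is below 5 points. A p-value above 0.05 would be easy to misread as support for the hypothesis. The quantity compared would also depend on the data and not on a decision made beforehand.

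**Working it through.** **Inputs.** From the protocol: MCID 5, SD 14.7, 98 per arm, Shapiro-Wilk at 5%, primary time point 12 months. Not in the protocol, hence assumed and varied: the 12-month mean and the shape of the scores.

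**What the sample size assumes.** The comparison of means has standardised difference 5/14.7 = 0.340. The usual formula gives n = 2 × (1.960 + 1.282)² × 14.7² / 5² = 182 per group, and 98 per group gives about 66% power. So the stated 98 does not reproduce. That is a separate matter and does not decide this point. What matters here is that the calculation is in mean DASH points.

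**How often the pre-test rejects.** Scores were simulated on 0-100 in steps of 100/120, with 98 per arm and 1,500 runs per setting. One shape was a scaled beta with SD 14.7. The other was a normal with SD 14.7 clipped to 0-100, where the mean shown is the one before clipping. The protocol does not say whether the test is run per arm or pooled, so both are given (% of runs rejecting).

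| Assumed mean | Beta, either arm | Beta, pooled | Clipped normal, either arm | Clipped normal, pooled |
|---|---|---|---|---|
| 5, 10, 15 | 100 | 100 | 100 | 100 |
| 20 | 100 | 100 | 98.5 | 99.9 |
| 25 | 99.9 | 100 | 50 | 82.5 |
| 30 | 90 | 98 | 14 | 17.5 |
| 40 | 28 | 36 | 10 | 4 |

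Up to a mean of about 20, the Mann-Whitney branch is practically certain under both shapes. From 25 upwards it depends strongly on the shape.

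**Whether the pre-test is needed.** With identical skewed arms (beta, means 5-20, SD 14.7), the t test's type I error stayed between 4.4% and 5.6%. At this size it needs no protection.

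**Whether a rank result can stand in for a mean difference.** With equal means of 10 but SDs of 14.7 and 11, Mann-Whitney rejected in 46-52% of runs and Welch's t test in about 5%. So the rank test can be significant when the mean difference is zero. With a true mean difference of 5 (beta, SD 14.7 in both arms, 800 runs):

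| Means | Average Hodges-Lehmann shift | Power, t test | Power, Mann-Whitney |
|---|---|---|---|
| 5 vs 10 | 2.1 | 68% | 100% |
| 10 vs 15 | 4.2 | 66% | 98% |
| 15 vs 20 | 5.1 | 68% | 86% |
| 20 vs 25 | 5.1 | 64% | 73% |

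Near the floor, even a rank-based shift in DASH points understates a 5-point mean difference. Further from the floor the two agree.

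**The case against.** The strongest reply has four parts.

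- **The branch is not certain.** A reader might infer that 12-month DASH must be skewed and that Mann-Whitney is all but guaranteed. The protocol gives no mean or shape, so this does not follow from it. A low mean a year after fixation of closed fractures is plausible but remains an assumption. This part stands, and the claim has to be conditional. It does not rescue the rule: where rejection is not near certain, the primary test is simply unpredictable.
- **Mann-Whitney does no inferential harm.** With identical arms its type I error was 4.5-5.3% in simulated skewed scores, and it had more power than the t test. This stands too. The defect lies in what is estimated and reported, not in an inflated error rate between identical arms.
- **The t-test branch names no confidence interval either, and the hypothesis is never tied explicitly to 5 points.** Both are true. A bare p < 0.05 criterion falls short on either branch. On the normal branch, though, the means are at least calculated, so a difference in points is available. A Hodges-Lehmann shift would also be in DASH points and the protocol does not forbid it, but none is planned, and it need not equal the mean difference.
- **Missing data.** Because DASH is collected four times, a reader might infer that visits are tested one at a time, that only patients with a 12-month score are analysed, and that the 12.5% assumed lost are discarded despite earlier scores. The article says none of this. It is silent on handling missing scores, which may be left to an analysis plan, and the 12.5% is only a planning allowance.

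**Conclusion.** The point holds in limited form. The analysis rule is stated in the text and is not an omission: a normality test decides whether the primary outcome is compared by means or by ranks, and the rank branch yields no estimate to set against the only threshold of clinical relevance the protocol gives. How likely that branch is depends on a 12-month mean the protocol does not state. With SD 14.7 and 98 per arm, it is about 98-100% for means up to 20, about 50-100% at 25 and about 14-90% at 30 (either arm rejecting, two assumed shapes). The first range applies if recovery is good. The documents do not support the unconditional reading, nor the reading that patients are dropped. This should be changed before analysis, but it does not undermine the trial's conduct or its data.

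**What to change.** In the Statistical analysis section, remove the normality pre-test for DASH. Prespecify one primary analysis: the difference in mean 12-month DASH between groups with its 95% confidence interval, from a t test or a linear model with robust or bootstrap standard errors, read against 5 points. Keep Mann-Whitney as a sensitivity analysis. A mixed model using the 1, 3, 6 and 12-month scores is optional and not needed to mend this point.

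The cost is wording, a registry update as the protocol foresees for modifications, and no new data. No interim analysis is planned, so the change can be made before outcomes are compared.

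There are two drawbacks. If scores are skewed and the arms differ in shape, the mean comparison can have less power than the rank test: about 64-68% against 73-100% for a 5-point difference in the beta simulations above. The interval will also be wide: at 98 per arm its half-width is 1.96 × 14.7 × √(2/98) = 4.1 points. It would lie wholly within ±5 only if the observed difference were below 5 − 4.1 = 0.9 points. The change lets the trial address its question but does not add precision.

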## Background

Both-bone forearm fractures are a common fracture, accounting for 3.4% of all paediatric fractures and 26% of paediatric upper extremity fractures [1, 2]. For children under 10 years old, most both-bone forearm fractures can be treated successfully with casting due to the considerable bone remodelling potential [3–5]. Although closed reduction and casting is a feasible choice for children older than 10 years old [6], there are adverse outcomes of conservative treatment, such as nonunion of the fracture, malunion and secondary surgery [7]. Also, the standard of amount of angulation or malrotation is not clear in this age group. In addition, for open fractures, fractures associated with compartment syndromes, elbow injuries, combined injuries such as Monteggia fractures and Monteggia equivalents, significant comminution or further displacement with nonoperative treatment, operative treatment is required [8–10]. For now, elastic stable intramedullary nailing (ESIN) and plate screw fixation are the common surgical procedures for paediatric both-bone forearm fractures [11]. The advantages of ESIN fixation for paediatric both-bone forearm fractures compared with plate fixation include less wound infection, shorter operative time, smaller edge, less soft tissue dissection, ease of implant removal and early return to activity after implant removal [12–16]. However, ESIN fixation also has its own shortcomings, including delayed union and nonunion, refracture, implant migration or failure and compartment syndrome [17–21]. Compared with younger children, the rate of complications is obviously increased in those over 10 years old [22–24]. Open reduction and internal fixation (ORIF) is a surgical alternative in this age group and offers some potential benefits, including immediate fracture stabilisation and anatomic reduction, which are important for restoring forearm rotation [25, 26]. However, ORIF has been criticised because of its longer operation time, the amount of soft tissue dissection and periosteal stripping, the increased amount of bleeding and the increased risk of wound infection [27, 28].

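### The primary 12-month DASH comparison uses no covariates, although age and AO fracture type are known at entry; prespecified adjustment would be a cheap gain in precision, of uncertain size

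*Protocol article*

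**What the plan says.** - **Outcome.** Primary outcome measures states "The primary outcome measure of this study is the DASH score" and "The primary time point is at 12 months". (The same section also lists radiological evaluation as primary; this point concerns DASH.)
- **Analysis.** Under Statistical analysis, a Shapiro-Wilk test decides the method for each continuous variable. If the variable passes, "the means will be calculated and compared using the independent samples" t test or ANOVA. If it does not, the Mann-Whitney U "test will be used for group comparisons". Neither branch names a covariate.
- **Variables known at entry.** Inclusion criteria admit ages 10 to 16 and two AO types, 22-A3 and 22-B3. Both must be established before a child can be randomised.
- **Randomisation.** Allocation and randomisation says "Patients will be randomly assigned to one of two groups (experimental or control) using a computer-generated random assignment in a 1:1 ratio". The method is to draw 112 of the numbers 1 to 224 for the hybrid arm. This fixes the arm sizes; no stratification or minimisation is described.
- **Precision target.** Sample size says "we used an α level of 0.05 and a β level of 0.1", "with a two-sided type I error rate of 5" percent, a 5-point minimal clinically important difference (MCID), an SD of 14.7 and 98 children per group.

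**The concern.** Two baseline characteristics that could plausibly relate to functional outcome are available for every child, yet neither the design nor the analysis uses them. Any DASH variance that they explain stays in the error term, so the confidence interval is wider than it need be.

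Precision matters more than usual here. The Background and Expectations sections look for no clinically relevant difference. That conclusion is credible only if the interval for the DASH difference is narrow compared with 5 points. A non-significant p value from a wide interval would not support it.

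There is also a practical risk. If the arms visibly differ in age or fracture type when the data are opened, the pressure to adjust will come after the results are known. Naming the covariates beforehand removes that choice.

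**Working it through.** **Inputs from the protocol:** difference 5 points, SD 14.7, two-sided alpha 0.05, 98 per group after losses, 112 per group recruited. **Assumption:** R², the share of 12-month DASH variance explained by age and AO type together. The protocol gives no figure, so a range is shown.

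**1. The protocol's own figure.** n per group = 2 × (14.7 × (1.960 + 1.282) / 5)² ≈ 182 (183 with the t distribution). The stated 98 does not reproduce for two independent groups at 90% power. The dropout step does: 98 / (1 − 0.125) = 112. With 98 per group, the noncentral-t power is 65.9%. This is the baseline for what follows.

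**2. Effect of adjustment.**
- Residual SD = 14.7 × √(1 − R²)
- Standard error of the difference = residual SD × √(2/98)
- Half-width of the 95% interval = 1.96 × standard error
- Equivalent unadjusted n per group = 98 / (1 − R²)
- Power from the noncentral t with effect size 5 / residual SD (the 2 degrees of freedom spent on covariates are ignored, which is immaterial with about 194)

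| Assumed R² | Residual SD | SE | 95% half-width | Power at 98 per group | Equivalent n per group |
|---|---|---|---|---|---|
| 0 | 14.70 | 2.10 | 4.12 | 65.9% | 98 |
| 0.02 | 14.55 | 2.08 | 4.07 | 66.8% | 100 |
| 0.05 | 14.33 | 2.05 | 4.01 | 68.1% | 103 |
| 0.10 | 13.95 | 1.99 | 3.90 | 70.4% | 109 |
| 0.15 | 13.55 | 1.94 | 3.79 | 72.9% | 115 |

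**3. What this means for the hoped-for conclusion.** The interval excludes a 5-point difference only if the observed difference is below 5 minus the half-width. That is 5 − 4.12 = 0.88 points unadjusted, and 5 − 3.79 = 1.21 points at R² = 0.15.

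**4. Chance imbalance at 98 per group (95% ranges).**
- AO type, if split 50/50 (assumption): 1.96 × √(0.25 × 2/98) = ±14 percentage points.
- Mean age, if uniform over 10 to 16 (assumption; SD 6/√12 = 1.73): 1.96 × 1.73 × √(2/98) = ±0.48 years.
- Resulting shift in the DASH difference: 1.96 × √R² × 14.7 × √(2/98), which is ±0.6, ±0.9, ±1.3 and ±1.6 points at R² of 0.02, 0.05, 0.10 and 0.15. The unadjusted standard error already contains this variation.

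**5. Could adjustment rescue the sample size?** For 98 per group to give 90% power, R² would have to be 1 − 98/181.6 = 0.46, about three times the top of the range above.

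**The case against.** **The prognostic premise is thin.** A reader might infer from the Background that age and fracture type span a wide prognostic range in this trial. The text does not support that. The sentence "Compared with younger children, the rate of complications is obviously increased in those over 10 years old" contrasts children over 10 with younger ones, so it is not a gradient within 10 to 16; it follows a list of elastic-nail shortcomings, and it concerns complications and not DASH. Significant comminution appears there only among the situations that call for surgery, and every child in this trial is operated on. Nothing links 22-A3 versus 22-B3 to outcome. This objection stands: the covariates are plausible, not shown to be prognostic, and the gain could be close to nil. At R² = 0.02 it is about one percentage point of power.

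**The unadjusted test is not wrong.** A reader might also infer that chance imbalance biases the result. It does not. The randomisation balances both variables in expectation, the type I error rate is preserved, and the standard error already allows for imbalance. This stands too, and is why the point concerns efficiency only.

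**Covariate lists are often left to the analysis plan.** That is fair in general, and a condensed article need not give one. Here, however, the article names the tests, and both are unadjusted, so a stated method is under review and not an omission.

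**Adding a covariate sentence is not enough.** Correct. A covariate model does not fit beside a rule that may switch to a rank test, so that rule has to change for the primary outcome as well.

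**Conclusion.** The point holds as a recommended improvement, not as a flaw in validity. The planned primary comparison is unadjusted, both covariates are known at entry, and the draw does not force balance on them. Under an assumed R² of 2% to 15%, adjustment raises power at 98 per group from about 66% to between 67% and 73%, and trims the 95% half-width from 4.12 points to between 4.07 and 3.79. These figures rest on the protocol's 5 points and SD of 14.7, on a linear-model analysis, and on an R² that the protocol does not supply. The low baseline comes from the sample-size calculation, which is a separate and larger problem that adjustment cannot repair.

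**What to change.** For 12-month DASH, replace the choice between t test and Mann-Whitney U by Shapiro-Wilk result with one prespecified linear model: DASH on treatment, age (continuous) and AO type (22-A3 versus 22-B3). Use robust or bootstrap standard errors if residuals are skewed. Report the adjusted difference with its 95% confidence interval as the primary result and the unadjusted comparison as supportive. Record the change before any outcome data are compared by arm.

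The cost is a short rewrite of the Statistical analysis section and 2 degrees of freedom, with no new data collection. The downside is that the gain may be negligible if the covariates turn out weak. The sample-size calculation needs its own correction.
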